**Fig. 1 Fig1:**
[figure not shown]
Randomization and data collection

The intervention group (IG) will receive usual care plus the educational intervention: “usual care” as described for the CG also applies to the IG. The intervention will consist of giving patients an opportunity to learn about the use of compression bandages, wearing and putting on compression stockings, physical activity, good skin care and a high-protein, vitamin-rich diet. This group will be supervised by another study nurse (not the nurse who is in charge of the control group).

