#### Exercises in the region of the lower extremities

Patients will be instructed to do regular foot and ankle exercises that can help strengthen the leg muscles and improve blood flow in the legs. While they are sitting (or standing), they have to flex their ankles by pointing their toes away from them and then pointing them up. Patients are instructed to do 10 repetitions of the exercise several times each day [41–43]. These exercises are consistent with the exercises in the guidelines for exercise and physical activity for older adults [44].

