#### Elevation

Patients will be advised to elevate their feet to heart level at least 2 h per day.

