## Methods: data collection, management and analysis

### Data collection

The feasibility (including acceptability) will be measured using the participation rate and the completeness and the acceptability of the intervention. The participation rate is the number of persons participating in the study divided by the number of persons eligible for participation. The completeness is measured by calculating the amount of missing data. The acceptability of the intervention is assessed from the data on self-care in patients with venous leg ulcers, physical activity and quality of life, food intake and nutritional status. The data from the intervention and control groups will be collected by each group’s own trained study nurse. Baseline data will be collected at the outpatient clinic whereas at T_1_, T_2_ and T_3_ the data will be collected during home visits.

At baseline (T_0_), basic demographic data such as age, sex, height, weight, marital status, socioeconomic factors and medical history will be recorded. Diagnostic information on the first occurrence of leg ulcers, venous interventions, deep-vein thrombosis, cardiac situation (chronic venous insufficiency (CVI) severity, Ankle Brachial Pressure Index (ABPI; ABPI = P_leg_/P_arm_), blood pressure, heart rate, edema) and other comorbidities will be obtained from the patient documentation on a single occasion. The data on self-care in patients with venous leg ulcers, physical activity and quality of life, food intake and nutritional status are obtained using instruments specifically validated for these concepts.

Health-related behavior is acquired monthly as a self-report (questionnaire) by the participants. The questionnaire enquires into the following parameters during the previous 24 h:Duration of wearing the compression stockings (in hours)Frequency and duration (time) of the elevation of the leg above heart level (minutes per day)Amount of physical activity (through a Fitbit)Number of foot exercises performed (how many days a week the foot exercises are performed)Nutrition (food intake assessment and nutritional status)Self-care

In addition, the following wound-related data are collected in patients with wounds:Date of recurrenceWound characteristics (size, time to possible healing, wound classification according to Widmer [46])Wound dressings used (including for compression)

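### Three self-report adherence items, as described, do not match their recall window, the open-ulcer population or the behaviour taught, and can return falsely low values

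*Protocol article*

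**What the plan says.** All references are to the protocol article.

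- **Timing and window** (Data collection): "Health-related behavior is acquired monthly as a self-report (questionnaire) by the participants". The items then follow under the stem "The questionnaire enquires into the following parameters during the previous 24 h".
- **Foot exercise**: the item is "Number of foot exercises performed (how many days a week the foot exercises are performed". The section on exercises in the region of the lower extremities says: "Patients are instructed to do 10 repetitions of the exercise several times each day".
- **Compression**: the item is "Duration of wearing the compression stockings (in hours". The eligibility criteria require an open venous leg ulcer. The description of the intervention group, below Fig. 1, says that patients will "learn about the use of compression bandages, wearing and putting on compression stockings". Data collection separately lists the dressings used, including those for compression, with no wearing time.
- **Elevation**: the item records the frequency and duration of "elevation of the leg above heart level (minutes per day". The Elevation section says: "Patients will be advised to elevate their feet to heart level at least 2 h per day".
- **Use of the data**: the Study objectives include comparing adherence with that of patients under standard care, and say that the pilot will inform the design of the main study.

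**The concern.** An adherence item is useful only if a patient who does what was taught gets a value that shows it. Here one item has a unit that its window cannot produce, one omits a form of compression that the protocol itself provides for, and one describes a different leg position from the one advised. In each case a patient can behave as instructed and still receive a low or uninformative value.

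The pilot is small (20 patients), so a few misrecorded zeros would visibly shift a group summary. Adherence is also the behaviour that the intervention is meant to change. If the items do not record it properly, the pilot's adherence figures are a poor basis for planning the main study.

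**Working it through.** The plan gives no figure to reproduce on this point. The check compares each item with its window, with the population and with the behaviour taught.

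**1. Foot exercise: window, title and unit**

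| Element | What it implies |
|---|---|
| Stem | previous 24 h |
| Title | a count of exercises |
| Unit in brackets | days per week, 0 to 7 |
| Taught behaviour | sets of 10 repetitions, several times each day |

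These cannot all hold. There are two readings:

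- *The stem governs.* A 24-hour window contains one day, so the item can only be 0 or 1. As an illustration, assume the window falls at random in the week. A patient who exercises on d days per week then shows none with probability 1 − d/7. For d = 5 this is 1 − 5/7 = 0.29; for d = 6 it is 1 − 6/7 = 0.14; for d = 7 it is 0.
- *The bracket governs.* The item runs from 0 to 7 and contradicts its stem, but gives no falsely low value.

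Neither reading records sets. Take three sets a day as an example of several (an assumption). A patient doing one set daily completes 7 × 1 × 10 = 70 repetitions a week, and a patient doing three completes 7 × 3 × 10 = 210. Both score 7 on the second reading and 1 on the first.

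**2. Compression: item and population**

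- Population: every patient has an open ulcer at entry.
- Taught content: bandages and stockings (text below Fig. 1).
- Wearing time collected: stockings only.
- Other record: dressings used for compression, without hours.

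A patient in bandages for the whole window who answers literally enters 0 h of stockings out of 24 h in compression. The dressing record may show that a bandage was used, but it cannot recover the hours. The article does not say how many patients will be in bandages, so the share affected may lie anywhere from none to all of those with open wounds.

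**3. Elevation: item and advice**

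- Advised: *to* heart level, at least 2 h × 60 = 120 min per day.
- Background section on leg elevation: also *to* heart level, 30 min three to four times a day, which is 30 × 3 = 90 to 30 × 4 = 120 min.
- Recorded: minutes *above* heart level.

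A patient who follows the advice exactly and answers literally enters 0 min instead of 120. A patient who treats the two phrases as equivalent enters 120. The wording does not settle which will happen.

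**The case against.** The strongest reply is that the questionnaire itself is not shown. The article gives a summary list of parameters, and the stem is clearly loose, since it also covers nutritional status and self-care, which are not 24-hour quantities. The natural reading is that the foot-exercise item carries its own weekly window. The stocking item fits the standardized session list and the section on putting on stockings, neither of which mentions bandages. Dressings used for compression are recorded separately. Patients may not distinguish *to* from *above* heart level. Finally, feasibility is judged mainly on participation and completeness, and the article plans between-group tests only at baseline.

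Much of this stands, and it limits the point. It shows that the stocking item is incomplete rather than inapplicable, and that the zeros depend on literal answers. It does not remove the mismatches: the article itself states the items, units and taught content, so condensation does not explain them. If the actual form is worded better, the protocol misdescribes it and still needs correcting.

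A reader might also infer more than the text supports:

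- *That correct behaviour is classed as non-adherence.* The article defines no adherence score or cut-off. The harm is a low or zero item value.
- *That the stocking item biases the comparison in favour of the intervention.* This would need the intervention to move patients from bandages to stockings. It is possible, because only that arm is trained in putting them on, but no section says that it will happen, and usual care is the same in both arms.
- *That every bandaged patient will record zero hours.* This assumes literal answering, no stocking use and no prompt about bandages on a form that is not shown.
- *That monthly 24-hour recall is itself the defect because it covers few days.* That coverage would be the same with perfectly worded items.

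**Conclusion.** The point holds as a measurement defect in three items as described. The foot-exercise item is internally inconsistent on any reading and omits sets per day. The compression item leaves time in bandages uncounted. The elevation item describes a different position from the one advised.

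For an individual, the possible error is as large as the item allows: 0 instead of 24 h of compression, or 0 instead of 120 min of elevation. Both rest on literal answers, and the compression figure also assumes bandages worn throughout. For the group, the size cannot be given, because the share of patients in bandages and the wording of the form are not stated.

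The items should be corrected because comparing adherence is a stated aim. The defect does not invalidate the pilot's participation and completeness measures. A spurious difference between arms remains a possibility and is not shown.

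**What to change.** Before the first patient:

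1. **Compression:** ask for hours in any prescribed compression, bandage or stocking, in the previous 24 h, and record the type.
2. **Foot exercise:** take the item out of the 24-hour stem and give it its own 7-day window. Ask for the number of days and the sets per day, and make the title agree with the unit.
3. **Elevation:** reconcile the Elevation section with the Data collection section, then word the item to match the advice that patients are finally given. Which position is right is for the clinical team to decide.

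The 24-hour window can stay for compression and elevation, since both quantities fit it. If the actual questionnaire already does these things, only the protocol text needs correcting. The cost is a minor rewording of three items and a slightly longer recall period for one of them.

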### Data management

The study nurse (SN) will collect the data on the intervention and control the accuracy of the documentation. Data entry will be performed using electronic support (EvaSys software) or paper format. The data quality assessment will be conducted in a cross-over procedure among the SNs.

Data entry will be checked for logical inconsistencies, extreme outliers, missing data and distributional properties. A random sample of 10% of all data entry forms will be checked. If the error rate is higher than 5% a second data entry will be performed.

All data will be kept in a cabinet in the project manager’s office at the School of Health Sciences, Geneva. Confidentiality will be assured. Only the investigators and the designated research team will have access to the data. Patient data will be coded, and the patient’s name and unique identifiers will not appear on any data forms. Links between ID and encoding will be accessible only with password restricted to the principal investigator. The Statistical Package for Social Sciences IBM SPSS 25.0 will be used for data analysis.

### Statistical methods

#### Univariate analysis

The sample (intervention and control groups) will be described, according to the data level, in terms of their demographic and health data, using descriptive statistics. Absolute and relative frequencies will be determined for categorical variables. Numerical averages and standard deviations will be calculated for normally distributed variables. The numerical median and IQR or range will be calculated for non-normally distributed variables. Exact 95% confidence intervals will be calculated where relevant. The calculations will be performed for each data acquisition time point.

#### Bivariate analysis

To compare the groups (intervention and control) at T_0_, a parametric test (*t* test) or a non-parametric test (Mann-Whitney U test) will be used for sociodemographic and health-related data depending on the data level and distribution. All tests will be two-sided.

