### Study objectives

The aim of the protocol is (1) to develop an interdisciplinary educational intervention (nursing, physical therapy and nutrition) and (2) to evaluate the feasibility of implementing it for patients with VLUs and compare their adherence to therapy to that among patients receiving standard care. The results from this pilot study will inform the design of the main study, which will measure the effectiveness of this interdisciplinary intervention.

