### Groups

A randomized controlled pilot trial with three measurement points will be carried out over 3 months to evaluate whether the intervention sustains an effect on the participants’ adherence to treatment. (Fig. 1). The control group (CG) will receive usual care. “Usual care” for patients in the CG is defined as follows: visits to the outpatient wound-care center as directed by a physician and wound care performed by the wound expert according to the hospital’s own standards. This standard corresponds to the one from the European Wound Management Association (EWMA).

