## Methods: assignment of intervention

### Randomization

After collection of baseline data, participants will be randomly assigned following simple randomization procedures (computerized random numbers) to one of two treatment groups. Gray sealed opaque numbered envelopes will be used. The intervention nurse will open the envelope and allocate the participant to the respective group.

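### The only planned between-group comparison is a significance test at baseline, before randomization; no between-arm estimate is planned for the adherence comparison that the aims call for

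*Protocol article*

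**What the plan says.** The Study objectives section pairs feasibility with a comparison between arms: the trial is to "compare their adherence to therapy to that among patients receiving standard care". The Groups section gives the randomized design with repeated measurement a purpose in the same vein: "to evaluate whether the intervention sustains an effect on the participants’ adherence to treatment". The Data collection section then provides for monthly self-report of stocking hours, leg elevation, activity, foot exercises, nutrition and self-care, with home visits at T1, T2 and T3.

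The analysis is set out in two short sections.

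- **Bivariate analysis.** "To compare the groups (intervention and control) at T_0_, a parametric test" or a Mann-Whitney U test "will be used for sociodemographic and health-related data depending on the data level and distribution". The section closes with "All tests will be two-sided". No other time point and no other between-group comparison is named.
- **Univariate analysis.** The two groups are described on demographic and health data by frequencies, means and SDs, or medians with IQR or range. "Exact 95% confidence intervals will be calculated where relevant", and "The calculations will be performed for each data acquisition time point".

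The Randomization section fixes the order of events: "After collection of baseline data, participants will be randomly assigned following simple randomization procedures".

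**The concern.** The one comparison between arms is made at a time when the arms do not yet exist. T0 precedes both allocation and education, so a difference found there cannot be an effect of the intervention. At the time points where an effect could appear, the article plans a description of each group but no contrast between them.

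Two things are at stake. First, baseline p-values invite wrong statements in the report: an imbalance declared because one of many tests fell below 0.05, or comparability declared because none did. Second, the pilot is meant to inform the design of the main study. That design would benefit from the between-arm adherence difference with its uncertainty and from the correlation of follow-up with baseline values. The analysis as written plans neither.

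**Working it through.** **Inputs.** The sample is 20 patients in two groups (Sample; Randomization). The article states neither alpha, the allocation ratio nor the number of baseline variables tested. I assume a two-sided alpha of 0.05, 10 patients per arm, and 10 to 20 independent baseline variables. Simple randomization does not guarantee a 10:10 split, so unequal splits are shown as well. The article gives no power calculation or other derived figure to reproduce.

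**1. Aims against analyses.**

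| Aim | Time at which it could be answered | Analysis planned then |
|---|---|---|
| Compare adherence between arms (Study objectives) | T1 to T3 | Per-group description only |
| Evaluate an effect on adherence (Groups) | T1 to T3 | Per-group description only |
| None stated | T0 | t test or Mann-Whitney U test between arms |

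The stated tests serve no stated aim, and the stated comparison has no matching between-arm analysis.

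**2. What the T0 tests can show.** Values recorded before a sound random allocation differ between arms only by chance. A simulation of 40,000 trials, each allocating 20 patients by simple randomization and applying a t test to a pre-randomization variable, rejected in 4.9%. That is alpha and nothing more. Over k independent tests the chance of at least one rejection is 1 − 0.95^k:

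- k = 5: 1 − 0.95^5 = 0.23
- k = 10: 1 − 0.95^10 = 0.40
- k = 20: 1 − 0.95^20 = 0.64

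Correlation among the variables would change these figures.

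**3. What a non-significant T0 test can show.** At 10 v 10, an observed imbalance of 0.5 SD gives t = 0.5/√(1/10 + 1/10) = 0.5/0.447 = 1.12 on 18 degrees of freedom, p about 0.28. An imbalance would have to reach about 2.10 × 0.447 = 0.94 SD before it was flagged. Non-significance therefore does not establish comparability.

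**4. What a follow-up estimate would give.** In SD units, the 95% half-width of a difference in means is t(0.975; n1 + n2 − 2) × √(1/n1 + 1/n2):

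- 10 v 10: 2.101 × 0.447 = 0.94
- 7 v 13: 0.98
- 8 v 7, after assumed losses: 1.12

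With adjustment for a baseline value that correlates r with follow-up, at 10 v 10, the half-width is approximately t(0.975; 17) × √(0.2 × (1 − r²)):

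- r = 0.5: 2.110 × √0.150 = 0.82
- r = 0.7: 2.110 × √0.102 = 0.67

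**5. Whether a follow-up test would be sensible.** At 10 v 10, a two-sided 5% t test has power of about 19% for a true effect of 0.5 SD and 40% for 0.8 SD. Power of 80% requires about 1.32 SD. A test of effect is not supportable; an estimate with its interval is.

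**The case against.** This is a 20-patient pilot. Its main yardsticks are participation, completeness of data and acceptability, and effectiveness is left to the later trial. Descriptive reporting after baseline is a defensible choice, and by the figures above the authors are right not to test for an effect. The article is also a condensed text, and the choice of model and covariates is commonly left to an analysis plan. All of this stands, and it lowers the weight of the point. It does not remove it: the article says which comparison will be made and when, and that choice does not match its own aims. A fuller plan could add the follow-up contrast, but the T0 tests would still need correcting.

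A reader might infer more than the text supports:

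- *The pilot would yield nothing useful on adherence.* Not so. If adherence counts as health data, the Univariate analysis section gives arm-level SDs at each time point, and a crude difference follows by subtraction. What is not planned is that difference with its uncertainty, or the baseline correlation.
- *The T0 tests carry no information of any kind.* They carry none on the intervention effect. The intervention nurse opens the envelopes, so a baseline difference could weakly hint at a failure of allocation. The article states no such purpose, and 20 patients give little power for it.
- *The 19% power at 0.5 SD is the chance of flagging a chance imbalance of that size.* It is not. That power refers to a true population difference, which sound randomization rules out at baseline. An observed imbalance of 0.5 SD is simply not significant, as step 3 shows.
- *The named tests are wrong for variables such as sex or marital status.* The section makes the choice depend on data level, so leaving a test for nominal data unnamed is ordinary condensation.
- *Three months is too short to speak of a sustained effect.* The article does not define the term, and repeated measurements can show persistence within that period.

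**Conclusion.** The point holds as a mismatch within the article. The only between-group comparison is fixed at T0, before randomization, while the aims need a comparison of adherence after it. For T1 to T3 only per-group description is planned. The timing conclusion rests on the text alone and on no assumed number.

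The 40% to 64% range for at least one spurious baseline finding depends on the assumed alpha and on 10 to 20 independent variables. The half-widths of about 0.94 SD unadjusted, and 0.82 SD at a baseline correlation of 0.5, depend on 10 v 10.

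This should be fixed, but it is not critical: the feasibility measures are unaffected, and no decision in the article depends on the baseline p-values.

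**What to change.** 1. In Bivariate analysis, delete the T0 significance tests and describe baseline by arm without p-values.
2. In their place, state that for each adherence measure the intervention-minus-control difference at T1, T2 and T3 will be reported with a 95% confidence interval, by randomized group. Adjust for the T0 value where that measure is collected before randomization. Label the results exploratory estimation without hypothesis testing.
3. In Groups, reword the purpose as estimating the adherence difference up to 3 months and its variability, for planning the main study.
4. State which adherence measures are recorded at T0. The article does not clearly place stocking hours, leg elevation or foot exercises there. The Fitbit is introduced as part of the intervention, so steps before randomization, and steps in the control arm, are not assured. Where no T0 value exists, report the unadjusted difference.

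The cost is a few sentences and a little extra analysis in SPSS. The intervals will be wide, and the report must say so, so that they are not read as evidence for or against an effect.
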